# Dynamic Interactive Social Cognition Training in Virtual Reality (DiSCoVR) for social cognition and social functioning in people with a psychotic disorder: study protocol for a multicenter randomized controlled trial

**DOI:** 10.1186/s12888-019-2250-0

**Published:** 2019-09-05

**Keywords:** Social cognition training, Virtual reality, Emotion perception, Theory of mind, Psychotic disorder, Social functioning

## Abstract

**Background:**

Problems in social functioning (e.g., unemployment, social isolation), are common in people with a psychotic disorder. Social cognition is a treatment target to improve social functioning, as it is a proximal predictor of social functioning. Social Cognition Training (SCT) improves social cognition, but may not generalize (enduringly) to social functioning, perhaps due to insufficient opportunity to practice in daily-life social situations. Using virtual reality (VR) for SCT could address this problem, as VR is customizable, accessible, and interactive. We will test the effect of a VR SCT, ‘DiSCoVR’, on social cognition and social functioning in a randomized controlled trial (RCT).

**Methods:**

In total 100 people with a psychotic disorder and deficits in social cognition will be recruited for this multicenter randomized controlled trial (RCT). Participants will be randomized to VR SCT (DiSCoVR) or VR relaxation training (VRelax; active control). DiSCoVR is a 16-session individual SCT, consisting of three modules: 1) emotion perception (recognizing facial emotions in a virtual shopping street); 2) social perception and theory of mind (observing social interactions between virtual characters and assessing their behavior, emotions and thoughts); and 3) application of higher-order social cognition in social interaction (role-playing personalized situations in VR). People receiving VRelax complete sixteen individual sessions, in which they receive psycho-education about stress, identify personal stressors, learn relaxation techniques, and explore relaxing immersive virtual environments.

Assessments will be performed at baseline, post-treatment, and 3-month follow-up. Primary outcomes are emotion perception (Ekman 60 Faces), social perception and theory of mind (The Awareness of Social Inference Test). Secondary outcomes include social functioning (Personal and Social Performance Scale), experiences and social interactions in daily life (experience sampling of emotions, social participation and subjective experience of social situations), psychiatric symptoms (e.g., depression, perceived stress, anxiety, positive and negative symptoms) and self-esteem.

**Discussion:**

To our knowledge, this will be the first RCT testing the efficacy of VR SCT. It will also investigate generalization to daily life social situations, the durability of treatment effects, and moderators and mediators of treatment success.

**Trial registration:**

On December 5, 2017, this trial was registered prospectively in the Dutch Trial Register as NTR6863.

**Electronic supplementary material:**

The online version of this article (10.1186/s12888-019-2250-0) contains supplementary material, which is available to authorized users.

## Background

For many people who have a psychotic disorder, it is a challenge to have meaningful daily activities, such as work, and to develop and maintain personal and romantic relationships; many of them experience problems in social functioning [1]. To function in daily life, it is necessary to adequately handle social situations and to be able to interpret the emotions, thoughts, intentions and behaviors of other people. These capabilities are generally referred to as *social cognition.* However, in people with a psychotic disorder, deficits in social cognition are common; a meta-analysis found large deficits in emotion perception and processing, social perception and theory of mind, compared to healthy controls [2]. Deficits in these key domains have been found to be important, proximal predictors for social functioning [3]. Social cognition has therefore become a target for psychosocial interventions aiming to improve social functioning through social cognitive training [4], a class of interventions also known as social cognition training (SCT).

SCT aims to improve social cognition, and ultimately social functioning through repeated practice with social stimuli (e.g., identifying emotions in pictures of faces), and compensatory strategy training (e.g., verbalization of salient facial features) [5]. A meta-analysis [6] of all types of SCT found large effects on emotion perception (recognition of emotions), and small to moderate effects on theory of mind (the ability to recognize and reflect on others’ mental states). A more recent meta-analysis [7], including only comprehensive forms of SCT (i.e., targeting multiple areas of social cognition), found a large effect on emotion perception and theory of mind, and a small to moderate effect on attribution style (judgments about the causes of events and others’ behavior). Together, these meta-analyses suggest that it is possible to improve social cognition with SCT in people with a psychotic disorder.

Some concerns have been raised, however, about the durability and generalizability of effects of SCT [4, 8]. While one meta-analysis [6] found a positive effect of SCT on community functioning, other reviews point out that treatment effects are most commonly and robustly found for lower-order social cognition processes such as emotion perception. On higher-order social cognition such as theory of mind, and social functioning, findings are more mixed and dependent on the specific measure used [4, 8]. We know from cognitive remediation research that integration with daily life is important for skills developed though cognitive training to generalize to social functioning [9]. Conventional SCT approaches may offer insufficient opportunity to practice in situations resembling real-life social interactions [8, 10]. Thus, effects of SCT on higher-order social cognitive processes and social functioning may be limited, as training materials may not sufficiently capture the complex, interactive and dynamic nature of real-life social situations.

The utilization of virtual reality (VR) for SCT has been proposed as a possible way to address this issue [4, 10]. VR is highly immersive, interactive and dynamic, and elicits psychological reactions similar to those in daily life [11]. Therefore, it is well-suited to simulate a variety of social situations and adequately reflect their complexity. At the same time, VR is controllable, which facilitates structured practice, and allows for situations to be scripted, repeated, varied, and personalized. Moreover, VR is a safe, accessible way to practice; participants know the virtual interactions can be stopped at any time, and that they can practice without negative repercussions and fear of embarrassment in their real social lives. Finally, VR is practical, as a wide range of situations can be generated quickly and practiced from one treatment setting, without traveling or accompanying participants in their daily environment.

VR is therefore a promising method to provide SCT. However, to our knowledge, no controlled studies of VR SCT for people with a psychotic disorder are available. Only one study on VR SCT has been published; a case report with two participants [12]. Improvements in social cognition and social functioning were reported after twenty sessions of a VR SCT. VR has also been used for social skills training (SST) in people with psychosis. A RCT of VR SST [13] among inpatients with schizophrenia (*n* = 91) showed that, compared to conventional SST, VR SST produced greater improvements in assertiveness and conversational skills, but no improvement was found in non-verbal skills. A pilot study of VR SST [14] reported improvement in social functioning, and VR measures revealed improvements in emotion perception, assertiveness, and time spent in conversations. Finally, pilot studies of VR SCT in people with autism spectrum disorder have reported improved emotion perception [15–17], attribution [16], theory of mind [15, 17], and (self-reported) social functioning [17]. Together, these studies suggest that VR SCT is promising.

To this end, we developed a novel VR SCT, Dynamic Interactive Social Cognition Training in Virtual Reality (DiSCoVR). In this randomized controlled trial (RCT), we aim to compare DiSCoVR to an active control condition, i.e., VR relaxation training (VRelax), in order to evaluate its efficacy on social cognition and social functioning. Moreover, we aim to assess the impact of the intervention on (the frequency and experience of) daily life social interactions, by using Experience Sampling Methodology (ESM), a diary method. We will also assess the durability of potential treatment effects in a 3-month follow-up period. Finally, we will perform moderator analysis to investigate who benefits from this VR SCT, and mediator analyses to examine variables mediating treatment effects. Thus, this study is the first RCT on VR SCT, using conventional measures of social cognition and functioning as well as experience sampling.

## Methods/design

### Participants

Participants are recruited from Dutch mental health treatment centers (University Center of Psychiatry of the University Medical Center Groningen, GGZ Drenthe, GGZ Delfland, and Zeeuwse Gronden). We recruit participants in two ways: 1) through advertisement of the study, by distributing posters and flyers, allowing participants to enroll themselves; and 2) through clinician referral: clinicians refer eligible and interested participants. Inclusion criteria are:
A diagnosis of a psychotic disorder according to DSM-5 criteria, either determined by a structured clinical interview (e.g., Mini-international Neuropsychiatric Interview [18], Structured Clinical Interview for DSM [19], Schedules for Clinical Assessment in Neuropsychiatry [20]) in the past three years or verified using the MINI Plus at baseline.Deficits in social cognition, as indicated by a clinician.Age 18–65 years.

Exclusion criteria are:
(Photosensitive) Epilepsy.An estimated IQ below 70, and/or a diagnosis of intellectual disability.Insufficient proficiency in the Dutch language.

Participants receive a compensation of €30 for each completed assessment, up to a total of €90. They also receive reimbursement for travel expenses incurred for the assessments.

### Design

The CONSORT inclusion flow diagram is shown in Fig. 1. This study is a multicenter single-blind randomized controlled trial (RCT) with two groups: 1) Dynamic Interactive Social Cognition Training in Virtual Reality (DiSCoVR), the experimental group; and 2) Virtual Reality Relaxation (VRelax), an active control group. Both groups receive treatment as usual alongside their designated intervention (DiSCoVR or VRelax). Participants complete three assessments: before the intervention (baseline, T_0_), directly after the intervention (post-treatment, T_1_) and three months after completing the intervention (follow-up, T_2_). After completion of the study, participants have the opportunity to receive the other treatment, if they wish.

**Fig. 1 Fig1:**
[figure not shown]
CONSORT flow diagram

### Interventions

#### DiSCoVR

DiSCoVR is a 16-session individual VR SCT, taking place twice a week over a period of eight weeks. DiSCoVR is provided by psychologists with (at minimum) a master’s degree in clinical psychology. A detailed treatment protocol describes the intervention, the software, the techniques that are used and the content of each session. Participants receive a workbook, containing session content summaries, exercises and worksheets (e.g., registration form of emotions they identified in their daily environment). DiSCoVR involves mass practice and compensatory strategy training. References to the patient’s personal situations and goals are made in examples and/or exercises whenever possible, to facilitate generalization of training material to daily life. To the same end, through homework exercises, participants are encouraged to practice with techniques and strategies they have learned in the intervention in daily life. These homework exercises are discussed at the start of each session. The intervention consists of three parts, structured to build upon each other in increasing complexity:
Module 1: Emotion perception (5 sessions, 1–5). Participants explore a virtual shopping street where they identify emotions on virtual characters’ faces. Several characteristics (e.g., intensity of emotions, time to respond) can be altered to adjust the difficulty level to the training needs of the participant. Participants practice with several strategies (e.g., mimicking emotions) to aid in emotion recognition, which they are encouraged to try at home.Module 2: Social perception & theory of mind (4 sessions, 6–9). Participants view scripted social scenarios in VR, about which open-ended questions regarding behavior, emotions and thoughts are asked. These questions aim to stimulate mentalization. Participants can respond by stating their answer out loud. If they answer incorrectly, characters will give more explicit hints about their mental state, with intensified emotional expression. Participants continue to apply social strategies to understand situations (e.g., remembering how you felt in a similar situation), by choosing a strategy before practicing in VR. Participants learn about the connection between thoughts, emotions and behavior, and practice with recognizing these in VR scenarios, themselves, and in others around them.Module 3: Social interaction (7 sessions, 10–16). Participants apply social cognitive skills in VR roleplay exercises with the therapist. They can practice with situations they struggle with, or that help them to achieve the goals they have set for the intervention. The protocol provides sample roleplay exercises, targeted at various social cognitive skills (e.g., detection of sarcasm and hints). Outside of VR, participants continue to practice with identifying emotions, thoughts and behavior and understanding their interrelatedness. They also learn a social problem-solving technique, in which they 1) consider their own thoughts, emotions and behavior; 2) consider the other person’s thoughts, emotions and behavior; 3) consider different possible ways to react to a situation; and 4) role-play the different reactions and choose the most appropriate reaction to carry out in real life. Participants continue to practice using strategies (e.g., watching someone’s emotional response to you to determine whether you should talk to them), both in VR and in real life.

The immersive VR worlds (a shopping street, a super market, an office and a bar), developed by CleVR BV, are displayed with an Oculus Rift headset (Consumer Version 1). They are shown in Fig. 2. Participants explore and interact with the virtual environment using a joystick controller. For the role play exercises, voice transformation is applied to mask the therapist’s real voice. During the role plays, therapists can click buttons on the computer interface to trigger emotions and/or gesture animations (e.g., shrugging, pointing) in their virtual character.

**Fig. 2 Fig2:**
[figure not shown]
Pictures of DiSCoVR environments and set-up. Legend: Top left: module 1 (translation: which emotion? Angry, happy, surprised); top right: module 2 (translation: what does Daniël actually mean?); bottom left: module 3, as seen from perspective of participant; bottom right: module 3, interactive role play setup. The virtual environments are property of CleVR BV; images have been used with permission from CleVR BV

#### VRelax

As an active control group, we chose VRelax, a VR relaxation therapy, as it matched important nonspecific characteristics of DiSCoVR (e.g., the use of VR, individual contact with a therapist twice a week), but did not target sociocognitive processes and therefore was not expected to improve social cognition. VRelax consists of sixteen sessions, provided twice a week in a period of eight weeks (the same as DiSCoVR), and aims to reduce both momentary (during sessions) and daily life stress and anxiety. VRelax is provided by therapists who either have 1) clinical experience in treating people with psychosis (e.g., psychiatric nurses); or 2) at least a bachelor’s degree in psychology. In VRelax, participants’ stressors are explored (i.e., which situations are stressful, and what are signs of stress). Participants learn to recognize stressful thoughts and rumination, and to apply coping strategies to address these (e.g., solving problems, asking for support and comfort, finding distraction). They also practice with relaxation exercises, such as breathing exercises, a body scan, grounding, and progressive muscle relaxation. Participants are encouraged to practice these techniques at home.

Each session starts with a discussion of stressors and negative emotions in the past few days. In some sessions, this is followed by psycho-education (e.g., about stress, coping and rumination). A large portion (±25 min) of each session is reserved for relaxation in VR. Immersive 360° video clips are shown with a Samsung Gear VR headset, running VRelax software developed by Viemr BV. Participants can visit a range of relaxing environments (Fig. 3), such as a sea in which they can swim with dolphins, a coral reef, a beach and a mountain meadow. They can control the environment using gaze; for example, to switch between environments or to engage with interactive elements (e.g., popping air bubbles underwater). Meditation exercises are embedded in the VR environment (e.g., guided meditation). Finally, part of each session is reserved for (learning to apply) relaxation techniques. These can be skipped if participants prefer to spend more time in VR.

**Fig. 3 Fig3:**
[figure not shown]
VRelax environments, including relaxation exercises. The virtual environments are property of Viemr BV; images have been used with permission from Viemr BV

### Materials and measurement instruments

The measures used in this study are summarized in Table 1.

**Table 1 Tab1:** Measures used in this study

Domain	Instrument	Method	Baseline (T_0_)	Post-treatment (T_1_)	Follow-up (T_2_)
*Primary outcome measures*					
Emotion Perception	Ekman 60 Faces (FEEST)	Picture task	x	x	x
Social Perception / ToM	TASIT-III	Video task	x	x	x
*Secondary outcome measures*					
Social functioning in daily life	Questions about social interactions, activities and momentary mental states	ESM questionnaire	x	x	x
Social functioning	PSP	Interview	x	x	x
Psychotic Symptoms	PANSS	Semi-structured interview	x	x	x
Social Anxiety	SIAS	Questionnaire	x	x	x
Paranoid Thoughts	GPTS	Questionnaire	x	x	x
Depression	BDI	Questionnaire	x	x	x
Anxiety	BAI	Questionnaire	x	x	x
Stress	PSS	Questionnaire	x	x	x
Self-esteem	SERS	Questionnaire	x	x	x
Information processing	TMT	Task	x	x	x
Demographic and clinical background	Questions	Interview	x	x	x
*Baseline diagnostic measures*					
Premorbid intelligence	NLV	Task	x		
Diagnostic	M.I.N.I. Plus	Structured Interview	x		
*Measures during sessions*			Session(s)		
Cyber sickness	SSQ	Questionnaire	S3		
Emotions	Questions	Questionnaire	VRelax: each session (2x)		
Performance on VR task	Social cognition tasks in VR	Task	DiSCoVR: S1–9		
Behavior in VR	Reaction time, interpersonal distance	Task	DiSCoVR: S1–9		

#### Primary outcome

##### Facial affect recognition

Ekman 60 Faces, Facial Expression of Emotions Stimuli and Tests (FEEST) [21]. 60-item computerized picture test assessing facial affect recognition. Participants view pictures of six emotions (happy, sad, angry, disgusted, surprised, anxious) and identify the expressed emotion. Total scores (0–60) are used for analysis.

##### Social perception and theory of mind

The Awareness of Social Inference Test part III (TASIT, Dutch version) [22, 23]. Short video clips showing social situations containing lies and sarcasm. Participants answer four questions after each video about the intentions, intended messages, beliefs and emotions of the characters. Total scores (0–32) are used for analysis. Parallel versions are used; the administration order (A-B-A or B-A-B) is randomized across participants.

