#### Randomization procedure

We utilized permuted block randomization with randomized block sizes (2, 4 or 6) using the R package ‘blockrand’ [34]. For each participating treatment center, we created strata for age (ten-year increments) and gender (i.e., ten strata per center). This resulted in a master randomization list with either ‘A’ or ‘B’ in each stratum. An independent employee then added an additional randomization by assigning DiSCoVR or VRelax to either A or B in the master randomization list using coin flips, once for each treatment center. Upon completing T_0_, the participants will be placed in the appropriate stratum in order of inclusion by the independent randomizer, determining their group assignment.

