#### Analysis

For our primary outcome variables (theory of mind and emotion perception), previous meta-analyses [6, 7] have found effect sizes ranging between moderate (*d =* .46, theory of mind) and large (*d* = .84, emotion perception). We therefore assumed a conservative effect size of .5. With β = .80, α = .05, two groups and three assessments, we found we would need 86 participants. Assuming a drop-out rate of 13% [35], we concluded that the sample should consist of 100 participants (50 in each group).

The groups will be compared at baseline using t-tests for normally distributed variables, and Mann-Whitney U-test or χ^2^ test for other variables. Variables with a significant baseline difference between the groups will be added to the analysis as a covariate.

We will use multilevel mixed-model linear regression analysis in accordance with the intention to treat principle, with repeated assessments (level 1) nested within participants (level 2). Time and group and their interaction term will be included as fixed effects. Treatment effects will be evaluated by examining the interaction between time and group. A random intercept will be included for the participant level to account for the repeated measures. A random slope will be included for time if this improves the model, according to the AIC value. The post-treatment and follow-up assessments will be analyzed separately, comparing each to the baseline. We will also perform a multilevel regression analysis on treatment completers, defined as people who have completed at least twelve sessions (75%) of their allocated intervention. Furthermore, moderator (e.g., clinical and demographic variables) and mediator analyses will also be conducted. Significance will be accepted at α = .05 (two-tailed); in case of multiple measurements within the same domain, a correction will be applied to α.

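### Every participant changes TASIT form between baseline and post-treatment, but the stated model has no form term, so any difference in form difficulty adds avoidable variance to a primary contrast

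*Protocol article*

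**What the plan says.** Under the primary outcome heading Social perception and theory of mind, the protocol article analyses the raw TASIT total and names two versions: "Total scores (0–32) are used for analysis. Parallel versions are used". On their sequence it says that "the administration order (A-B-A or B-A-B) is randomized across participants". It states no equating step and no figure for the equivalence of the versions.

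The Analysis section describes one mixed model for the outcomes: "Time and group and their interaction term will be included as fixed effects". For the random part, "A random intercept will be included for the participant level to account for the repeated measures", with a random slope for time if AIC favours it. The contrasts are set as follows: "The post-treatment and follow-up assessments will be analyzed separately, comparing each to the baseline". The one rule for further covariates is "Variables with a significant baseline difference between the groups will be added to the analysis as a covariate".

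Under Randomization procedure, treatment allocation is stratified by center, age and gender. TASIT order is not a stratum.

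**The concern.** Under A-B-A or B-A-B, nobody takes the same form at T0 and T1. If one form is harder, each participant's T0–T1 change carries the whole difficulty difference, with a plus sign for one order and a minus sign for the other. The design itself introduces this variation and the order is known for every participant, yet the stated model leaves it in the residual.

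Nothing else in the model takes it out:

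- The participant intercept cannot, because the effect reverses sign within the person.
- A random slope for time would only relabel it as between-person variation in change.
- The covariate rule cannot either. A time-constant order covariate, even if order met the significance criterion, does not remove an effect that changes sign between visits.

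At stake is the precision of the post-treatment contrast, which the Discussion puts first among its hypotheses. Theory of mind is also the domain with the smaller of the two effect sizes cited in the Analysis section (d = .46 against .84).

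**Working it through.** **Inputs from the article.** Effect size 0.5, two-sided alpha .05, power .80 (printed as β), 86 evaluable participants or 43 per arm, 13% drop-out, 100 randomized.

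**Assumed, because the article does not give them.** The difficulty difference between forms, δ, in SD units of the TASIT total; the T0–T1 correlation, r; the two orders split 50:50.

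**The plan's own figure.** A between-groups repeated-measures F test with f = 0.5/2 = 0.25, three assessments and an assumed correlation of 0.5 has noncentrality 0.25² × 86 × 3 / (1 + 2 × 0.5) = 8.06. Power is .801 at N = 86 and .792 at N = 84, so 86 is reproduced. Then 86/0.87 = 98.9, consistent with 100. The form question does not alter these figures.

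**Variance of the T0–T1 change (SD² units).**

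- With form fitted: 2(1 − r).
- With form left out: 2(1 − r) + δ², because each change contains +δ or −δ with equal frequency.
- Proportional increase: δ² / [2(1 − r)].

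| δ | r = .5 | r = .6 | r = .7 |
|---|---|---|---|
| .2 | .04/1.0 = 4% | .04/0.8 = 5% | .04/0.6 = 7% |
| .3 | .09/1.0 = 9% | .09/0.8 = 11% | .09/0.6 = 15% |
| .5 | .25/1.0 = 25% | .25/0.8 = 31% | .25/0.6 = 42% |

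**Power for a 0.5 SD effect** (two-sample noncentral t on the change score, 43 per arm, r = .6):

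| δ | Variance of change | Power, form left out |
|---|---|---|
| 0 | 0.80 | .727 |
| .2 | 0.84 | .706 |
| .3 | 0.89 | .681 |
| .5 | 1.05 | .609 |

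A normal approximation gives values about .01 higher (.736, .716, .691, .619) and the same losses.

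**Chance imbalance in order.** If the proportion of one order differs between arms, the contrast moves by 2δ times that difference. The SD of this shift is 2δ × √(2 × 0.25/43), or 0.04, 0.06 and 0.11 SD for δ = .2, .3 and .5. Its square is 2δ²/43. That is exactly what δ² adds to the squared standard error of the contrast, 2[2(1 − r) + δ²]/43. Imbalance and noise are therefore one quantity and must not be counted twice.

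**Type I error.** In simulation (10,000 trials per setting, r = .5, 43 per arm, δ from 0 to .5) the rejection rate under no effect was .048 to .052 without form and .048 to .051 with it. Simulated power at δ = .5 was .54 without form and .63 with it.

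**T0–T2.** Each participant takes the same form at both visits, so δ cancels from the change.

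**The case against.** **The article is condensed.** It gives one generic model for all outcomes, and an instrument-specific covariate is often left to an analysis plan. That plan is not shown and may already contain form. The stated list of fixed effects is also not declared closed. This stands as a limit: the point applies to the model as the article states it. It is more than silence, however, because the article sets out both the form-switching schedule and a model, and the covariate rule it gives could not absorb the effect.

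**Randomizing the order already protects the comparison.** This is right as far as validity goes. A reader might infer that form differences bias the treatment effect, or that chance imbalance in order is a further harm on top of the noise. The documents support neither. Order is randomized, so the estimate is unbiased in expectation and type I error holds, and the imbalance is already part of the added variance.

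**No form difference is documented.** This also stands. The only indication in the article is the word parallel, which points towards a small difference. At δ = .2 the loss is about two power points, and the larger figures rest on assumption. The label is nevertheless not evidence of equal difficulty in this population.

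**Follow-up.** A reader might extend the point to T2 and ask for form in that model as well. With complete data, a participant-level form covariate leaves the T0–T2 time-by-group estimate unchanged. Nor does the article plan a formal comparison of the T1 effect with the T2 effect.

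**Conclusion.** The point holds as one of precision, confined to the T0–T1 contrast of the TASIT. The stated model leaves a known, randomized design factor in the residual of a primary contrast. How much that costs depends on δ, which the article does not give. It is nothing if the forms are truly equivalent, slight at δ of .2 or less, and worth having from about .3 SD upwards. There is little power to give away: on the change score with 43 per arm and no form effect at all, power is .727 at r = .6, below the planned .80. These sizes rest on the assumed r and δ, an even split of orders and a change-score approximation to the mixed model.

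**What to change.** In the TASIT T0–T1 model, prespecify the form taken at each assessment (A or B) as a time-varying fixed effect. With two visits this is the same as an order-by-time term. Leave the T0–T2 model as it is.

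The cost is one sentence of analysis text and one degree of freedom. No new data are needed, because the form taken follows from the randomized order. Writing it down before the analysis also avoids a post hoc decision should the orders turn out unevenly split between arms. If an analysis plan already includes form, nothing further is required.
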